#### Study procedures

The protocol structure follows the Standard Protocol Items: Recommendations for Interventional Trials (SPIRIT) 2013 statement. The SPIRIT schedule with a complete overview of the study procedures for this trial is summarized in Fig. 2. The complete SPIRIT checklist for the study is provided in Additional file 1.

**Fig. 2 Fig2:**
[figure not shown]
Standard Protocol Items: Recommendations for Interventional Trials (SPIRIT) figure with overview of the study procedures

### Statistical analysis

#### Sample size calculation

A total sample size of 66 is needed. It will allow detection of a significant difference between morphine plus placebo and morphine plus gabapentin groups in mean pain scores at EOS. Mean baseline pain scores of 8.5 are assumed for both groups, with estimated EOS pain scores of 5.4 for morphine alone versus 4.5 for morphine plus gabapentin based on percentage change in pain scores in a previous trial in adults [31].

A minimum number of patients is defined per age group: (1) at least 5 patients aged 3 months to less than 3 years, (2) at least 15 patients aged 3 years to less than 7 years, and (3) at least 20 patients aged 7 years to less than 18 years. No maximum number of patients per age group is specified. A two-tailed test will be applied with a significance level of 0.5 and a power of 80%, and 10% dropout is anticipated.

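### The two-tailed significance level is printed as 0.5, most likely a misprint for 0.05, and with no SD given the article cannot show which level produced the 66 patients

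*Protocol article*

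**What the plan says.** The section on sample size calculation in the protocol article asks for 66 patients in total and gives these planning values:

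- Baseline: "Mean baseline pain scores of 8.5 are assumed for both groups".
- Effect: "estimated EOS pain scores of 5.4 for morphine alone versus 4.5 for morphine plus gabapentin", a difference of 0.9 points. The source is described as "based on percentage change in pain scores in a previous trial in adults".
- Test, level, power and loss: "A two-tailed test will be applied with a significance level of 0.5 and a power of 80%, and 10% dropout is anticipated".

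No SD is given for the end-of-study pain score. The section on type of analysis sets a superiority comparison by ANCOVA, with baseline pain score, centre and age group in the model, and names no significance level. The abstract and the discussion restate the primary comparison, also without a level. The 0.5 is therefore the only significance level in the article.

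**The concern.** A two-sided level of 0.5 means that, if gabapentin adds nothing to morphine, the test still declares a difference half of the time. No confirmatory reading of a double-blind superiority trial can rest on that.

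A dropped zero is usually harmless, because the remaining inputs give back the printed sample size at 0.05 and so show what was meant. Here that check cannot be made: the SD is the one input missing. What is at stake is the decision rule for the primary test as printed, and whether the claimed 80% power belongs to a test at 0.05.

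**Working it through.** **Inputs from the article**

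- Difference: 5.4 − 4.5 = 0.9 points.
- Allocation 1:1 (section on randomization), 66 randomised, 33 per arm.
- Dropout 10%: 66 × 0.9 = 59.4, so about 59 evaluable, taken as 30 + 29.
- Power 80%, two-tailed.
- SD: not stated. Because the primary analysis adjusts for baseline, the relevant SD is the residual one.

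**Step 1. Can 66 be reproduced?** Not from the stated inputs, because the SD is missing. The calculation can only be run backwards, to find the SD that 66 implies at each level.

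**Step 2. Implied SD, normal approximation.** SD = 0.9 / [(z for the level + z for the power) × √(1/30 + 1/29)], with √(1/30 + 1/29) = 0.2604.

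- Level 0.05: 0.9 / [(1.960 + 0.842) × 0.2604] = 1.23.
- Level 0.5: 0.9 / [(0.674 + 0.842) × 0.2604] = 2.28.

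**Step 3. Implied SD, noncentral t on 57 degrees of freedom.**

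- Level 0.05: SD 1.21.
- Level 0.5: SD 2.36.

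If all 66 were evaluable (33 + 33), these become 1.29 and 2.50. Each value is an upper limit, since a smaller SD gives more power.

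**Step 4. Power at 0.05 with 30 + 29 evaluable.** The noncentrality is 0.9 / (SD × 0.2604). The SDs are an assumed range, since the article gives none. The last column is the difference detectable with 80% power, 0.9 × SD / 1.213.

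| Assumed residual SD | Power at 0.05 | Detectable difference |
|---|---|---|
| 1.0 | 92% | 0.7 |
| 1.2 | 81% | 0.9 |
| 1.5 | 62% | 1.1 |
| 2.0 | 40% | 1.5 |
| 2.5 | 27% | 1.9 |

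**Step 5. Residual against raw SD.** Raw SD = residual SD / √(1 − r²), where r is the baseline to outcome correlation (assumed). A residual SD of 1.23 corresponds to a raw SD of 1.42 at r = 0.5 and 1.72 at r = 0.7. A limit of about 1.2 on the residual SD is therefore less tight than it looks if read as a limit on the raw SD.

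**The case against.** The strongest answer is that this is a dropped zero. Nobody plans a superiority trial with a 50% type I error, the figure stands in the sample size section rather than in the description of the primary analysis, and an analysis plan that is not shown may set the level. The article also condenses a fuller protocol, so the SD may be stated there or in the cited adult trial, and its absence here is no fault in itself.

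Most of this stands. The 0.5 is best read as a misprint, and the missing SD is not raised as an omission of its own. It matters only because it is the figure that would show what the misprint stands for. What does not stand is that the error can be left alone: a wrong level is printed, and nothing else in the article corrects it.

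Two stronger readings are tempting, and the article supports neither.

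- A reader might infer that 66 was actually computed at 0.5. With the SD unknown, some SD fits 66 at any level, so the fit at 0.5 is no evidence that 0.5 was used.
- A reader might infer that the trial is underpowered, with true power of 27% to 40%. That needs a residual SD of 2.0 to 2.5, which appears nowhere in the article. Baseline adjustment, and averaging twice-daily scores over three days, both tend to lower the relevant SD. If 0.05 was used with a residual SD of about 1.2, the stated 80% holds and the only defect is the printed figure.

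**Conclusion.** The printed significance level is wrong as it stands, by a factor of ten if 0.05 was meant, and it is the only one in the article. That much is certain; that 0.05 was intended is a judgement, though a safe one.

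The 80% power is unverified rather than refuted. It holds at 0.05 if the residual SD is no more than about 1.2 points. If 66 did come from a calculation at 0.5, the implied residual SD is about 2.4, and power at 0.05 with that SD would be about 30%. The article does not say which case applies. These figures assume a two-group comparison with 59 evaluable patients, equal SDs and a 0.9-point difference.

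The correction is required because it concerns the decision threshold of the primary test and costs almost nothing.

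**What to change.** 1. Correct the level to 0.05 two-sided in the sample size section, and state the same level for the primary ANCOVA.
2. Give the residual SD used for 66 and its source, confirming that 66 follows at 0.05 with 80% power and 10% dropout.
3. If it does not follow, print the power, or the difference detectable with 80% power, that 66 randomised (about 59 evaluable) deliver at 0.05 with that SD.

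The cost is one corrected number and a sentence or two. No extra patients and no change of design are needed. The article's section on trial status reports that no patient has yet been included, so the correction can precede all data. The only possible price is a less favourable power statement.

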#### Type of analysis

The primary efficacy analysis of this study is aimed at assessing the superiority of treatment with morphine and gabapentin compared with morphine and placebo. The hypothesis to be tested is that the average pain scores (average of two measures each day for 3 days before EOS visit V10) assessed by age-appropriate pain scales (FLACC, FPS-R, NRS-11) are lower in the treatment group (morphine + gabapentin) than in the control group (morphine + placebo).

The primary analysis of efficacy will be conducted using one-way analysis of covariance (ANCOVA) with baseline average pain score as a covariate. Other covariates will include center, treatment, and age (three subgroups). A second ANCOVA model including a treatment × center interaction term will be used to assess consistency across sites.

Intergroup differences as breakthrough pain and frequency and dosage of rescue medication will be assessed using sample *t* test or Wilcoxon-Mann-Whitney tests.

Statistical analysis will be performed using IBM SPSS Statistics 21 (IBM, Armonk, NY, USA) or SAS 9.4 (SAS Institute, Inc., Cary, NC, USA) software for PC.

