#### Outcome measurements

The primary outcome of the study is the average pain score (defined as average pain score of twice-daily assessments of 3 consecutive days) at the end of the study period in both treatment groups. Secondary endpoints are percentage of responders with 30% reduction in pain score, average daily pain intensity by age-appropriate scale, observational pain assessment with use of NRS-11 by parents/caregivers and investigator at each visit, number of episodes of breakthrough pain > 4/10 pain score and use of rescue medication, number of rescue interventions, number of pain-free days with < 4/10 pain score without rescue medication, participant dropouts due to lack of efficacy, total cumulative weight dose of each rescue drug, quality of life scored with the PedsQL at baseline (V2) and EOS visit (V10), acceptability of treatment (Facial Hedonic Scale) at EOS visit, global satisfaction with treatment (NRS-11 completed by parent/patient) at EOS visit, CGI-S at V6 and EOS (CGI-S by investigator), patient/parent PGIC at V6 and EOS, PK parameters: apparent clearance (CL/F), apparent volume of distribution (Vd/F), absorption rate constant (Ka), area under the curve (AUC), maximum (peak) concentration (Cmax), time of maximum concentration (Tmax), concentration at steady-state (Css), minimum concentration (Cmin) incidence of adverse events, percentage of adverse events, percentage of subjects discontinuing the trial due to adverse events, aggressive behavior in children > 6 years old (Retrospective-Modified Overt Aggression Scale) at V2–V6 and EOS, and suicidal ideation (C-SSRS) at V1 and EOS.

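### Breakthrough and rescue endpoints are totals compared by unadjusted two-sample tests with no allowance for days observed, so unequal dropout makes the arm observed for fewer days look better than it truly is

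*Protocol article*

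**What the plan says.** Under Outcome measurements, the secondary endpoints include "number of episodes of breakthrough pain > 4/10 pain score and use of rescue medication, number of rescue interventions", then "number of pain-free days with < 4/10 pain score without rescue medication" and "total cumulative weight dose of each rescue drug". Each is worded as a number or a cumulative total over the child's time in the trial. The same list contains participant dropouts due to lack of efficacy.

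Under Type of analysis, one sentence covers the comparison: "Intergroup differences as breakthrough pain and frequency and dosage of rescue medication will be assessed using sample" *t* test or Wilcoxon-Mann-Whitney tests. It names no days observed, rate, offset or covariate. It does not mention pain-free days. The primary ANCOVA in the same section does adjust for age group, and Randomization is stratified by age group.

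Under Efficacy measurement, pain during the trial is scored each morning and whenever breakthrough pain is noticed, and the diary records rescue medication. Follow-up is 3 weeks of dose optimization plus 12 weeks of maintenance. The Abstract says that groups are compared by intention to treat, so early leavers stay in the comparison.

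Under Sample size calculation: "A two-tailed test will be applied with a significance level of 0.5 and a power of 80%, and 10% dropout is anticipated". The planned means are "estimated EOS pain scores of 5.4 for morphine alone versus 4.5 for morphine plus gabapentin", from a baseline of 8.5.

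**The concern.** A child who leaves at week 4 can contribute only four weeks of episodes and rescue doses. On endpoints where a low total is a good result, leaving early lowers the total whatever the child's daily rate was. A *t* test or Wilcoxon test on such totals compares burden and time observed together.

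The direction depends on who leaves. If more placebo children leave for lack of efficacy, placebo totals are too low and a real benefit of gabapentin is masked. If more gabapentin children leave for adverse events, the benefit is overstated. These endpoints are meant to support a primary result based on three days of scores at the end of the study, so a distortion in either direction matters for interpretation.

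A second, smaller matter is what the breakthrough count measures. The score of 4 lies below the mean pain that the plan expects in both arms at the end of the study.

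**Working it through.** The plan gives no figure for these endpoints, so there is none to reproduce. The check asks how far totals move when the true daily rates are equal.

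**Inputs from the protocol article.** Follow-up is 21 + 84 = 105 days. N is 66 at 1:1, so 33 per arm. Dropout is 10% overall. **Assumed:** the split of dropout between arms and its timing. A split of 5% versus 15% averages to the planned 10% and is about 2 versus 5 children of 33. A split of 10% versus 30% averages 20%, above plan, and is a stress case.

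**Expected days observed** with dropout proportion d and mean exit day e: (1 − d) × 105 + d × e. Uniform exit gives e = 52.5. Exit spread over the titration weeks gives e = 10.5. With equal daily rates, the ratio of totals equals the ratio of days (arm with more dropout divided by the other).

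| Dropout | Exit | Expected days | Ratio of totals |
|---|---|---|---|
| 10% vs 10% | same timing | equal | 1.00 |
| 5% vs 15% | uniform | 102.4 vs 97.1 | 0.949 |
| 5% vs 15% | day 28 | 101.15 vs 93.45 | 0.924 |
| 5% vs 15% | titration | 100.3 vs 90.8 | 0.906 |
| 10% vs 30% | uniform | 99.75 vs 89.25 | 0.895 |
| 10% vs 30% | titration | 95.55 vs 76.65 | 0.802 |

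Example, day 28: 0.95 × 105 + 0.05 × 28 = 101.15 and 0.85 × 105 + 0.15 × 28 = 93.45. Timing alone also matters: 10% dropout in both arms, uniform in one and in titration in the other, gives 95.55 / 99.75 = 0.958. Pain-free days shrink by the same proportions, but there a lower count is the worse result.

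**Effect on the test.** A simulation used 33 per arm, gamma-Poisson counts with mean 0.7 per day and shape 2 (both assumed), equal true rates and 1,500 runs. At 5% versus 15%, Wilcoxon rejected in 7% (uniform) or 10% (titration) of runs on totals, and in 5–6% on per-day rates. At 10% versus 30%, it rejected in 10% or 27% on totals and 4–6% on rates. With 10% in both arms it rejected in about 5% either way.

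**If leavers have twice the daily rate.**
- Uniform exit: a leaver's expected total is 2 × 52.5 = 105, the same as a completer's, so the totals are equal (ratio 1.00). The true ratio of mean daily rates at 5% versus 15% is 1.15 / 1.05 = 1.10. The simulation gave 1.02 for totals and 1.12 for rates. (Averaging ratios over runs adds 1–2% even when nothing differs.) The worse arm's disadvantage is hidden, but that arm does not come out ahead.
- Exit in titration: (0.85 × 105 + 0.15 × 21) / (0.95 × 105 + 0.05 × 21) = 92.4 / 100.8 = 0.92, so the totals still favour the arm with more dropout.

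**Cut-off.** 4.5 − 4 = 0.5 and 5.4 − 4 = 1.4, so the cut-off is below both planned means. No SD is stated. Reading the printed significance level as 0.05, an SD of 1.24 gives n = 2 × (1.96 + 0.84)² × 1.24² / 0.9² ≈ 30 per arm, or 60 in total; 60 × 1.1 = 66 and 60 / 0.9 ≈ 67. With that SD and a normal distribution, about 66% of gabapentin and 87% of placebo children would have an average end-of-study score above 4. Over assumed SDs of 1.0 to 2.5, the ranges are 58–69% and 71–92%.

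**The case against.** The strongest reply is that the article is silent rather than wrong. Frequency of rescue can mean a rate, either test can be run on per-day values, and a statistical analysis plan that is not available here may supply the denominator, the rule for choosing between the two tests and any covariates. Part of this stands: the article does not exclude a per-day analysis, and leaving age out of a secondary comparison costs precision without invalidating it. But the endpoint definitions are in the article, and they say number and total cumulative dose. Read together with the named tests, the plan as printed compares totals.

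A reader might infer that the arm with more dropouts will look better than the other arm. The documents do not support that. No split of dropout is given, and the bias vanishes if dropout is equal in amount and timing. If leavers have a higher daily rate and leave throughout follow-up, the totals come out about equal.

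A reader might also infer that ordinary background pain will be counted as breakthrough. That does not follow either. The endpoint wording can be read as requiring rescue use as well as a score above 4, and scores outside the morning are taken when breakthrough is noticed. The percentages above describe children's average end-of-study pain, not the share of episodes that are spurious. The Discussion justifies 4 as the point at which pain needs treatment, which fits a count of treated pain.

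Finally, the trial is described as exploratory, and dropout for lack of efficacy is reported as its own endpoint, so an imbalance would be visible. That limits the harm but does not correct the comparison.

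**Conclusion.** The point holds in a limited form. The count and cumulative-dose endpoints are tied to unadjusted two-sample tests with no stated allowance for days observed, in a trial that foresees early exit. With equal true rates and an assumed 15% versus 5% dropout, totals in the arm observed for fewer days are about 5–9% too low, and the Wilcoxon false-positive rate is about 7–10% instead of 5%. Larger distortions need dropout above the planned 10%. The pull is always towards the arm with fewer days on episodes and rescue, and against it on pain-free days. Whether that arm ends up ahead depends on who leaves and when. The primary ANCOVA and the sample size of 66 are not affected.

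On the cut-off, the comparison of numbers is exact: 4 is below 4.5 and 5.4. The consequence is one of description. The endpoint cannot be presented as a rise above background pain.

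**What to change.** In Type of analysis, replace the sentence on breakthrough and rescue with the following:

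- Analyse the number of breakthrough episodes and the number of rescue interventions by negative binomial regression with log(days observed) as offset, and with treatment and the age stratum used at randomization as terms.
- Analyse the dose of each rescue drug as mg/kg per day observed.
- Analyse pain-free days as a proportion of days observed.
- Report dropout for lack of efficacy, by arm, beside these results. A per-day rate assumes that a leaver's observed days represent that child's burden, and readers need to see how many leavers there were.

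In Outcome measurements, describe the breakthrough endpoint as episodes of pain > 4/10 treated with rescue medication, and do not present it as a rise above background pain. No new threshold is proposed.

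The cost is mainly wording, and the article states that no patient had yet been included. Rescue use is already a diary item, and pain is already scored each morning and when breakthrough is noticed. The first and last observed day of each child must be available in the data. The downside is small: a model replaces a simple test, and per-day rates from children who leave early are noisier.

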#### Pharmacokinetic-pharmacodynamic analysis

PK data will be analyzed by nonlinear mixed effects modeling with NONMEM (version 7.2; ICON Development Solutions, Dublin, Ireland) to estimate PK parameters, including volume distribution, clearance of gabapentin and morphine, and variability and precision. Also, influence of potential covariates will be evaluated.

Using predicted drug concentrations, a population PK-pharmacodynamic (PD) model will be developed to link drug exposure to pain response.

### Ethical approval

Ethical approval was obtained from the Medical Ethical Committee of the Erasmus Medical Centre, Rotterdam, The Netherlands.

Medical ethical review is under way in the other participating centers (EudractCT, 2014-004897-40), and the study is registered at ClinicalTrials.gov (NCT03275012).

### DSMC

The study safety and progress will be reviewed by an independent data and safety monitoring committee (DSMC) according to the DSMC charter. All adverse effects reported by the subjects or observed by investigators or staff will be recorded. A continuous evaluation will be performed by an independent DSMC. In case of disproportionate adverse effects or prolonged inclusion, the DSMC can decide to terminate the study. No interim analysis for efficacy is planned.

## Discussion

The GABA-2 study is an exploratory, randomized, double-blind, placebo-controlled, multicenter study designed to evaluate the efficacy of gabapentin added to morphine in pediatric patients with severe neuropathic or mixed pain.

Although strong opioid use for benign pain is met with cultural barriers in many countries, the use of morphine is recommended by the WHO guidelines for persistent pain in children as a first-line treatment [30]. Also, the use of morphine for NP is questioned by practitioners, but tramadol and morphine have shown efficacy in several randomized controlled trials concerning different types of NP [3–5, 32] and are therefore advised in the guidelines from the International Association for the Study of Pain for the treatment of NP in adults [32, 33].

Hence, the use of morphine for severe NP in children should be seriously considered and studied clinical trials. Because treatment with first-line agents such as antidepressants and anticonvulsants as monotherapy for severe NP is not always sufficient [34], and because data show a synergistic effect of gabapentin when added to morphine in adult patients with NP, this design was chosen for the children with the most severe pain (pain scores 7 or higher on a scale of 0–10).

Although opioids other than morphine, based on PD properties, might be more suitable [8], they were considered inappropriate for this study because of unavailability in some of the participating countries.

Chronic pain, specifically NP in children, is often difficult to treat. Children are often undertreated owing to a lack of evidence or medication is used off-label because it often is not registered for use under a certain age. For example, in The Netherlands, gabapentin is not registered for treatment of NP in patients younger than 12 years. Moreover, high-quality studies investigating the efficacy and safety of gabapentin for this indication in children are lacking. Hence, we believe our trial is necessary and timely.

Pediatric PK studies of gabapentin [35, 36] have shown that oral clearance of gabapentin was directly proportional to creatinine clearance, which is higher for children younger than 5 years of age than in older children and highly variable in infants younger than 1 year of age. Therefore, a PK analysis was performed by simulating different dosing scenarios to evaluate dosing requirements to ensure effective drug concentrations of gabapentin as described in treatment of adult NP [37]. Based on this analysis, an appropriate dosing schedule based on weight bands for practical considerations will be used.

Justification of this dosing regime will be further investigated by assessing drug exposure using sparse sampling techniques. A correlation between exposure and analgesia will be explored.

The dosing regimen for morphine and slow-release morphine is based on the WHO guideline for morphine in children [30], and it will be titrated on the basis of tolerability in the first days of the active treatment phase of the trial. Slow-release morphine with lower daily dosage would be the preferred formulation, but it is not available or registered for all age groups. Therefore, depending on the body weight of the patient as well as on availability and registration in the participating countries, immediate-release formula or tablet morphine is chosen for the titration phase. Slow-release morphine is chosen for patients above 30 kg during the maintenance period of the study.

The primary endpoint of the study will be the differences in average pain scores for the two treatment groups (average of two measures each day for 3 days before the EOS visit) assessed by the age-appropriate pain scales (FLACC, FPS-R, NRS-11). Because the age range of the study population is wide, different pain scores were needed to ensure the most optimal scale for the different age groups. FLACC is a validated, observer-based scores for younger children. For school-age children, the FPS-R was chosen as a validated self-reported pain score, whereas the NRS-11 was considered most appropriate for older children. We realize that these scores are only validated for acute pain, but in the absence of validated pain tools for chronic pain, these scores were considered the best validated alternatives. Another limitation is that the data need to be analyzed in an aggregate way (i.e., all age groups together). For this reason, we also used scores that are expressed on a 10-point scale and can be analyzed together, although we acknowledge that cross-validation of the absolute scores has not been done, to our knowledge. In general, a pain score of 4 is accepted as a cutoff for pain that needs treatment for all scores; hence, we considered the combined use of scores acceptable.

To our knowledge, this is the first randomized controlled trial studying the effectiveness of the combination therapy morphine and gabapentin for pain in children. Although very challenging in design and in potential recruitment and retention of patients, we believe this trial will provide more solid evidence of the efficacy of gabapentin in combination with morphine to ultimately improve the treatment of severe NP in children.

